### Outcomes

The primary outcome is the change in total blind rated PANSS total scores at 12 weeks from baseline.

Secondary outcomes include: blind rated change in overall Clinical Global Impression Scale (CGI) [48], clinician rated level of adherence (CRS) [49], adverse effects (GASS-C) [50], health-related quality of life (EQ-5D-Y) [51], subjective experience (DAI-10) [52], readmission rate, (EI-AD-SUS) [53], and change in PANSS sub-scale (positive, negative and general) [44]. We will also combine these outcomes (EQ-5D-Y and total PANSS score) with service use data (EI-AD-SUS) to compare treatments on cost-effectiveness.

Patients will be followed up for 12 months with the potential for further follow-up using clinical records for longer-term evaluations.

For the mechanistic study, outcomes include the change in brain glutamate, regional cerebral blood flow (rCBF) and GSH, and peripheral cytokines and GSH from baseline to 12 weeks.

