#### Mechanistic study

Brain Magnetic Resonance Imaging (MRI) scans and blood samples will be acquired at baseline and 12 weeks. MRI data will be acquired at 3 Tesla at 3 centres, and will include proton magnetic resonance spectroscopy (1H-MRS) to measure levels of glutamate, GSH and other brain metabolites visible in the 1H-MRS spectrum in voxels positioned in the bilateral anterior cingulate cortex and right striatum, arterial spin labelling to measure rCBF and T1-weighted structural brain images to provide anatomical localisation, grey matter masking of rCBF images and correction of 1H-MRS data for voxel tissue composition. The blood samples will be used to measure levels of peripheral pro- and anti-inflammatory cytokines and GSH.

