### Sample size

The standardised mean difference for clozapine versus other antipsychotics in adults based on PANSS total score at 12 weeks is 0.39 [55]. The standard deviation of the PANSS score at 12 weeks in our similar sample of treatment resistant patients being started on clozapine [43] is 14.2 (60% CI 12.96–16.20). Using an upper limit of the 60% confidence interval [56], an effect size of 0.39 corresponds to a between group difference of 6.4 points. In our previous research [43], the 95% CI for the baseline-12-week correlation in the sample was 0.553 to 0.880, and we use a value of 0.5. This is conservative but realistic, since the time points are only 12 weeks apart. Under these assumptions, and assuming 20% attrition to 12-week follow-up, the target sample size to recruit at baseline is 260 participants.

For the mechanistic study we estimate that, of all participants recruited at MRI sites, 50% will agree to participate in MRI. This results in a sample for the mechanistic study of 90 participants at baseline and, assuming 20% attrition, complete mechanistic data in 70 participants. This sample size has 80% power to detect a minimum between group effect size of 0.7SD on a standardised scale and 90% power for 0.8SD. In our previous observational study in TRS [43], we found a within-group effect after 12 weeks of clozapine of 0.7. Assuming there is no further change from prior treatment in the standard antipsychotic treatment arm on these measures over 12 weeks, we would have sufficient power to detect between-group effects of these magnitudes and expect the effect sizes to be greater in the younger population.

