### Randomisation

Participants will be randomised 1:1 using an online system hosted by the King’s Clinical Trials Unit, using computer generated blocks of random sizes. The sample will be stratified by sex and age group (< 18 years, >  = 18 years).

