Analyses will be conducted in Stata version 17or later. Descriptive statistics within each randomized group will be presented for baseline values. For the primary analysis, the treatment effects on primary and secondary outcomes will be estimated using linear mixed models fitted to all outcome variables up to and including the 12-week assessment. Fixed effects will be sex, age (< 18, >  = 18) and duration of previous treatment (± 3 years), baseline assessment for the outcome under investigation, treatment, time, and time*treatment interactions. Participant will be included as a random intercept to account for repeated measures. Marginal treatment effects will be estimated for primary outcome (PANSS score at 12 weeks), and for PANSS scores at each other time point (6 weeks, 12 weeks), and reported separately as adjusted mean differences in scores between the groups with 95% confidence intervals and 2-sided p-values. For secondary outcomes the same approach will be followed using linear mixed models to estimate and report the treatment effect at each time point. Cohen’s D effect sizes will be calculated as the adjusted mean difference of the outcome divided by the sample standard deviation of the outcome at baseline. These will be displayed in a forest plot showing the treatment effects on the primary and the secondary outcomes at 12 weeks. For the secondary analysis including 24-and 52-week time points, we will repeat the linear mixed model approach with these additional outcomes in the response vector. We will report the estimated marginal treatment effects at 24-and 52-weeks.

Missing data on individual measures will be pro-rated if more than 80–90% (depending on questionnaire) of the items are completed; otherwise, the measure will be considered as missing. We will check for differential predictors of missing outcomes by comparing responders to non-responders on key baseline variables. Any significant predictors will be included in the analysis models in a sensitivity analysis. This accounts for missing outcome data under a missing at random assumption, conditional on the covariates included in the model. As a sensitivity analysis, we will assess whether treatment adherence is associated with missing data, and if it is associated, use inverse probability weights or multiple imputation to compare results.

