A pre-specified subgroup analysis will test the treatment effect in children (age < 18 years) by estimating the effect in each group separately. If the final proportion of under 18 s is low, we may use a Bayesian subgroup analysis to increase precision of the effect in the groups. There are no planned interim analyses.

For the mechanistic study, descriptive statistics for biomarkers at baseline and 12 weeks will be presented by treatment group. We will test for between-group differences on peripheral cytokines, GSH, brain glutamate and rCBF at 12 weeks using appropriate generalised linear models. Mechanistic analyses will be based on causal mediation analysis and the primary outcome variable will be the PANSS total score at 12 weeks. We will estimate the direct and indirect effects of clozapine on total PANSS via the mechanistic measures by fitting models for the outcome with and without mediators using the difference in coefficients approach, extended for multiple mediators. We will adjust for baseline values of the mediators [58] baseline PANSS total score, and fixed effects of sex, age, duration and number of previous treatment trials [59].

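### The between-group biomarker tests at 12 weeks name no baseline covariate, although the outcomes are defined as change and the baseline values are collected; naming it would gain precision at no cost

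*Protocol article*

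**What the plan says.** All references are to the protocol article.

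- **Outcomes** defines the mechanistic endpoints as changes: "For the mechanistic study, outcomes include the change in brain glutamate, regional cerebral blood flow (rCBF) and GSH, and peripheral cytokines and GSH", measured from baseline to 12 weeks. The mechanistic hypothesis under Aim and objectives is also worded as reductions and increases over that period.
- **Assessments, Mechanistic study** provides both measurements: "Brain Magnetic Resonance Imaging (MRI) scans and blood samples will be acquired at baseline and 12 weeks".
- **Statistical analysis** describes the group comparison as: "We will test for between-group differences on peripheral cytokines, GSH, brain glutamate and rCBF at 12 weeks using appropriate generalised linear models". No covariates are listed for it. The same paragraph then turns to causal mediation for total PANSS and closes with an adjustment for baseline mediator values, baseline PANSS, sex, age and treatment history.
- **Statistical analysis**, for the primary and secondary outcomes, lists the baseline value of the outcome among the fixed effects. The mechanistic outcomes are not named there.
- **Sample size** states for the substudy: "This results in a sample for the mechanistic study of 90 participants at baseline and, assuming 20% attrition, complete mechanistic data in 70 participants". It continues: "This sample size has 80% power to detect a minimum between group effect size of 0.7SD on a standardised scale and 90% power for 0.8SD". A baseline-to-week-12 correlation (0.5) is given for PANSS only.

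**The concern.** The outcome is a change, the baseline is measured, and the clinical models use it. The one analysis that addresses the mechanistic outcomes directly is described as a comparison at 12 weeks with no baseline term. A statistician following that sentence literally would compare 12-week levels.

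The cost would be precision. Part of the spread in a 12-week biomarker level is stable difference between people that was already present at baseline. A baseline covariate removes it, which matters with about 35 people per arm.

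There is a second, smaller cost. Three analyses remain open for several biomarkers: 12-week level, change score, and baseline-adjusted level. They differ in power and can give different p-values on the same data, so the choice is best fixed before data split by arm are seen.

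**Working it through.** **Inputs**

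- 70 participants with complete data (Sample size).
- 1:1 allocation: "Participants will be randomised 1:1 using an online system hosted by the King’s Clinical Trials Unit". This gives about 35 per arm.
- Effects of 0.7 SD and 0.8 SD (Sample size).
- Two-sided 5% level. This is an assumption for the biomarkers, carried over from the PANSS analysis, which is to be "reported separately as adjusted mean differences in scores between the groups with 95% confidence intervals and 2-sided p-values".
- Correlation r between baseline and 12-week biomarker: not given. I assume 0.3, 0.5 and 0.7.
- The 0.7 SD is read as SDs of the 12-week value. The article speaks only of a standardised scale.

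**Step 1: the plan's own figure.** Take a two-sample t-test with no covariate, 35 per arm, 68 degrees of freedom and noncentrality d × √(35/2).

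- d = 0.7: noncentrality 0.7 × 4.183 = 2.93, power 82.3%.
- d = 0.8: noncentrality 0.8 × 4.183 = 3.35, power 91.0%.
- Detectable effect: 0.68 SD at 80% power and 0.79 SD at 90% power.
- Total needed: 68 for 0.7 SD at 80%, and 68 for 0.8 SD at 90%.

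The stated 70 participants and the 80%/90% figures are therefore reproduced with no baseline covariate.

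**Step 2: add the baseline of the same biomarker.** The residual SD becomes SD × √(1 − r²), so the effective standardised difference is 0.7 / √(1 − r²), with 67 degrees of freedom.

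**Step 3: an unadjusted change score for comparison.** The SD of the change is SD × √(2(1 − r)), so the standardised difference is 0.7 / √(2(1 − r)), with 68 degrees of freedom.

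| r (assumed) | Baseline-adjusted: effective d | Power | Detectable at 80% (SD) | Change score: effective d | Power |
|---|---|---|---|---|---|
| no adjustment, 12-week level | 0.70 | 82.3% | 0.68 | n/a | n/a |
| 0.3 | 0.7/0.954 = 0.73 | 85.7% | 0.65 | 0.7/1.183 = 0.59 | 68.4% |
| 0.5 | 0.7/0.866 = 0.81 | 91.5% | 0.59 | 0.7/1.000 = 0.70 | 82.3% |
| 0.7 | 0.7/0.714 = 0.98 | 98.1% | 0.49 | 0.7/0.775 = 0.90 | 96.1% |

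The adjusted analysis is ahead of both alternatives in every row. The change score falls below the plain 12-week comparison when r is under 0.5 and equals it at 0.5. Taking the word change in the Outcomes section as an instruction to analyse unadjusted differences could therefore lose power.

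**Step 4: scope of the closing baseline sentence.** It follows the description of direct and indirect effects on PANSS by the difference-in-coefficients approach, calls the biomarkers mediators, and lists baseline PANSS alongside them. Those features fit a model with PANSS as the response. It names no model, however, so its reach is not settled by the text.

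**The case against.** The strongest reply is that nothing in the article says baseline is left out. A generalised linear model can take covariates, and the sentence lists none at all, not even the stratifiers. The article promises a separate analysis plan and points to a fuller protocol, and a covariate list may properly sit there. The document also uses 12-week wording for PANSS and still adjusts for its baseline. This stands: omission is an inference from silence, and the point is about wording. It does not remove the contrast within the article, which names covariates for the clinical models and the mediation models but not for this comparison.

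A reader might infer three stronger things that the documents do not support:

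- **That the substudy is underpowered.** The planned power is met with no adjustment (step 1). Any loss is relative to a better analysis that is available.
- **That the power statement proves an unadjusted analysis.** It shows only that no correlation was used in the calculation, which may be a conservative simplification. The 0.7 SD itself is justified from a within-group effect over 12 weeks.
- **That chance baseline imbalance biases the test.** Under 1:1 randomisation it adds variance that the standard error already reflects.

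It is also fair to object to imposing an ordinary linear model on every biomarker. Cytokines and metabolites may need a different link or a transformation, and the plan's flexibility on this should stay.

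**Conclusion.** The point holds as a low-cost improvement in precision and clarity. The between-group biomarker tests are described without a baseline term, while the outcome definition, the data collection and the clinical models all point to using one. The closing baseline adjustment most naturally covers only the mediation models.

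If the text is followed literally, the power forgone at 0.7 SD is about 3 percentage points at r = 0.3 (82.3% to 85.7%), 9 at r = 0.5 (to 91.5%) and 16 at r = 0.7 (to 98.1%).

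These sizes rest on assumed correlations, on 35 complete pairs per arm, on a two-sided 5% level, and on 0.7 being in SDs of the 12-week value. That adjustment does not lose to the unadjusted comparison holds across the whole assumed range. If baseline is already in the full protocol or analysis plan, nothing is lost and only the article's wording needs aligning.

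**What to change.** State in the analysis plan that each between-group biomarker comparison at 12 weeks is a generalised linear model, with a link or transformation suited to that biomarker, and that it includes treatment arm, the baseline value of the same biomarker (on the matching scale), and the stratifiers sex and age group. Say that this is how the change outcome in the Outcomes section is estimated, and that an unadjusted change score will not be substituted. Say also whether the baseline adjustment closing the mechanistic paragraph applies to the mediation models only.

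The cost is a sentence or two of wording, settled before anyone sees biomarker data split by arm. It needs no new data and no change to the sample size; the extra covariates use three degrees of freedom out of 68. The stated 80% and 90% power can stay as they are.

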### Aim and objectives

The purpose of the trial is to assess whether clozapine is more effective than TAU (standard antipsychotics) in young people with TRS in real-world settings, over a 12-week period, at the level of clinical symptoms, patient-rated outcomes, quality of life and cost-effectiveness. The primary objective is to compare the treatments on the change in total Positive and Negative Syndrome Scale (PANSS) [44] score from baseline to 12 weeks. The secondary objectives are to compare the treatments on function, adverse effects, quality of life, subjective improvement, and cost-effectiveness.

In the CLEAR trial the following hypotheses will be tested:Primary hypothesis: clozapine will be more effective than TAU after 12 weeks of treatment as demonstrated by reduction in PANSS total scoresSecondary hypotheses:Clozapine will lead to a higher global improvement than TAU as measured by the CGI at 12 weeks, 24 weeks, and 52 weeksClozapine will lead to a better improvement in health-related quality of life than TAU as measured by EQ-5D-Y at 12 weeks, 24 weeks, and 52 weeksClozapine will be cost-effective compared to TAU at 12 weeks, 24 weeks, and 52 weeksThe prevalence of adverse effects in participants on the clozapine arm will be higher than TAU at 12 weeks as measured by the GASS-C, weight, and metabolic laboratory measurements (i.e., higher HbA1C and lipids)The clozapine arm will be more likely to remain on the same medication longer-term than TAU, as measured by medication use at 24 weeks and 52 weeks.Mechanistic hypotheses:Improvement in schizophrenia symptom severity during clozapine treatment compared to TAU will be mediated by anti-inflammatory and glutamatergic mechanisms. The biomarkers characterising these anti-inflammatory and glutamatergic mechanisms will include reductions in peripheral proinflammatory cytokines (e.g., IL-6), brain glutamate and rCBF, and increases in anti-inflammatory cytokines (e.g., IL-10) and peripheral and central oxidative defence (GSH) from baseline to 12 weeks.

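### Scanner or site is missing from the listed mediation covariates although the MRI mediators come from three centres, which can bias the indirect effect through them

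*Protocol article*

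**What the plan says.** Protocol article, Mechanistic study (under Assessments): "MRI data will be acquired at 3 Tesla at 3 centres". MRI "scans and blood samples will be acquired at baseline and 12 weeks". The scanner supplies brain glutamate, brain GSH and rCBF. The remaining mediators come from blood: "The blood samples will be used to measure levels of peripheral pro- and anti-inflammatory cytokines and GSH".

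Protocol article, Statistical analysis: direct and indirect effects on 12-week PANSS total are estimated by fitting outcome models with and without the mediators, "using the difference in coefficients approach, extended for multiple mediators". The adjustment set is then given: "We will adjust for baseline values of the mediators [58] baseline PANSS total score", followed by "fixed effects of sex, age, duration and number of previous treatment trials". It contains no scanner, site or centre term, and the article states no harmonisation step.

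Protocol article, Randomisation: "The sample will be stratified by sex and age group". Site and scanner are not strata.

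Protocol article, Aim and objectives: the mechanistic hypothesis concerns movement in the biomarkers, for example "peripheral and central oxidative defence (GSH) from baseline to 12 weeks".

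**The concern.** Three centres mean, in practice, three scanners, and scanners can read systematically higher or lower than one another. Such an offset moves the measured mediator without any change in the patient. Randomisation keeps the comparison of arms on the mediator unbiased, but it does not protect the step from mediator to PANSS. An offset unrelated to PANSS acts as measurement error in the mediator and weakens its coefficient. If patients at the three sites also differ in PANSS, scanner is a common cause of measured mediator and outcome. In either case the drop in the treatment coefficient when the mediator is added, which is the planned estimate of the indirect effect, can be wrong.

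At stake is the mechanistic conclusion: how much of clozapine's effect runs through glutamate, central oxidative defence or blood flow. The article fixes the covariate list in some detail, down to the number of previous treatment trials, yet leaves out a technical factor that its own design creates.

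**Working it through.** **The plan's own figure.** Sample size states 70 completers, with 80% power at 0.7 SD and 90% at 0.8 SD. With 35 per arm and two-sided 5% (assumed), the noncentral t gives 82.3% and 91.0%. The detectable effects are 0.68 SD at 80% and 0.79 SD at 90%, which round to the stated 0.7 and 0.8. The statement reproduces.

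**Set-up for the bias.** Within arm, let the true mediator have variance 1 at each visit and correlation *r* between visits. Each scanner adds a constant offset *u* with variance *s*, the same at both visits (one scanner per centre and per participant, assumed). PANSS depends on the 12-week mediator (*b*), the baseline mediator (*g*) and the offset (*h*, which stands for site differences in PANSS). None of these values is in the documents. One mediator is considered at a time.

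Each measured mediator has variance 1+*s* and their covariance is *r*+*s*. The coefficient of the 12-week mediator, adjusted for baseline, is

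[(1+s)(b+gr+hs) − (r+s)(br+g+hs)] / [(1+s)² − (r+s)²] = [b(1+r+s) + (h−g)s] / (1+r+2s).

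The treatment effect on the mediator is unbiased under randomisation, so dividing by *b* gives the share of the true indirect effect that is recovered.

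**Level carries the effect, offsets unrelated to PANSS (g = h = 0).** The share is 1 − s/(1+r+2s). With offsets 0, +k and −k SD, s = 2k²/3 for equal thirds. For site shares of 60/25/15%, s = (0.40 − 0.10²)k² = 0.39k².

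| k | Site shares | s | r = 0.3 | r = 0.7 |
|---|---|---|---|---|
| 0.5 | 60/25/15 | 0.0975 | 0.93 | 0.95 |
| 0.5 | thirds | 0.167 | 0.90 | 0.92 |
| 1.0 | 60/25/15 | 0.39 | 0.81 | 0.84 |
| 1.0 | thirds | 0.667 | 0.75 | 0.78 |

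For example, k = 1, thirds, r = 0.3: 1 − 0.667/2.633 = 0.75. The understatement is 5-10% at 0.5 SD and about 15-25% at 1.0 SD, with the baseline mediator already in the model.

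**Other structures, r = 0.5.**

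| Assumption | s = 0.1 | 0.25 | 0.5 | 1 |
|---|---|---|---|---|
| Level only (g = h = 0) | 0.94 | 0.88 | 0.80 | 0.71 |
| Partly change (g = −b/2, h = 0) | 0.97 | 0.94 | 0.90 | 0.86 |
| Pure change (g = −b, h = 0) | 1.00 | 1.00 | 1.00 | 1.00 |
| Sites differ in PANSS (g = 0, h = 2b) | 1.06 | 1.13 | 1.20 | 1.29 |
| Sites differ in PANSS (g = 0, h = −b) | 0.88 | 0.75 | 0.60 | 0.43 |

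**Simulation check.** 72 participants, three equal scanners, 4,000 replicates, r = 0.5 or 0.8, difference-in-coefficients estimator. At s = 0.25 and r = 0.5 the listed model recovers 0.87 (level), 1.005 (pure change) and 1.14 (h = 2b), against 0.875, 1.00 and 1.125 from the formula. With scanner indicators added, recovery is 0.995 to 1.006 in every scenario run.

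**Bias against sampling error.** In the level-only case at r = 0.5, the SD of one estimate, as a share of the true effect, is 0.40 without and 0.42 with the scanner term at s = 0.25. Root mean squared error is √(0.13² + 0.40²) = 0.42 without and 0.42 with, so nothing is lost. At s = 1 it is √(0.28² + 0.37²) = 0.46 without and 0.42 with.

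**The case against.** Four points have force.

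First, the baseline mediator is already in the model and the hypothesis is worded as change. If change alone drives PANSS there is no bias at any offset size. That stands as one case. But the planned model estimates the baseline coefficient freely, and with offsets unrelated to PANSS any value between pure level and pure change leaves some attenuation.

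Second, a reader might infer that the bias is always towards zero. The documents do not support this: pure change gives none, and site differences in PANSS can push it either way. Central blinded PANSS rating and adjustment for baseline PANSS should limit such differences, but patient mix may still vary by site.

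Third, a reader might infer that the between-group biomarker tests fall below the stated 80% power. A wholly unadjusted 12-week test would drop to 76-79% (0.5 SD offsets) or 61-69% (1.0 SD). But the article does not say that those tests omit baseline; it leaves the choice of generalised linear model open, and Outcomes defines the measures as change. With baseline adjusted, power at 0.7 SD is 83-98% (0.5 SD) and 78-98% (1.0 SD), below 80% only for equal thirds, 1.0 SD and r = 0.3. That inference should not be drawn.

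Fourth, the SAP and full protocol are not shown and may add the term, and in a sub-study of about 70 people sampling error exceeds a 5-10% bias. Both are true. They lower the weight of the point but do not remove it, because the article states a specific list and scanner is not on it.

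**Conclusion.** The point holds in limited form. The listed mediation covariates omit scanner or site, and used as written they can bias the indirect effect through brain glutamate, brain GSH and rCBF. The bias is often towards zero: about 5-10% at 0.5 SD offsets and 15-25% at 1.0 SD, if offsets are unrelated to PANSS and the 12-week level carries the effect. In the scenarios with site differences in PANSS, the recovered share runs from 0.43 to 1.29.

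These figures rest on assumed offsets, site shares and correlations, and on one unchanged scanner per participant, so the actual bias cannot be quantified from the documents. Mediators measured in blood are outside the point. The stated power for the mechanistic study is not called into question. This is a cheap improvement to a secondary analysis, not a flaw in the primary one.

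**What to change.** Add scanner as a three-level fixed effect to the mediation models that use an MRI measure. Put it in both the outcome model with the mediators and the one without, so that the difference in coefficients reflects the mediators alone. Add the same term to the between-group models for brain glutamate, brain GSH and rCBF. Models with blood mediators only need no change. If the SAP already does this, confirming it is enough.

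The cost is one line of wording and two degrees of freedom out of about 70 (2/70 = 2.9%), in line with a simulated variance penalty of roughly 3% when there is no offset. The centre of each scan is known, so no new data are needed. Specifying the term now also avoids a choice made after the data are seen. It deals with constant offsets; a participant who changes scanner between visits would need to be flagged.
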